#### **Adverse Event**

An Adverse Event (AE) is defined as any untoward medical occurrence, unintended disease or injury, or untoward clinical signs (including abnormal laboratory findings) in subjects, users or other persons.

**NB!** This includes any and all events related to the study device, the comparator or the procedures involved.

**NB!** For users or other persons, this definition is restricted to events related to the study device.

#### **Causality**

The investigator is responsible for determining whether there is a causal relationship between an AE and the use of a medical device.

All AEs are categorized as unrelated, possibly related or related, as defined below:

- **Unrelated:** the AE is not reasonable in relation to the use of the medical device, or another cause can itself explain the occurrence of the event.
- **Possibly related:** the AE may be explained by the medical device and the onset is reasonable in relation to the use of the medical device, however there is insufficient information to determine the likelihood of this possibility.
- **Related:** the AE is most likely explained by the medical device and the onset is reasonable in relation to the use of the medical device.

An AE that is categorized as being **related** to the use of a medical device constitutes an ADE.

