## 1.2 Risk/Benefit Assessment

There are several side effects or problems reported with the use of TAI, though most of them are mild and of minor concern. These complications should be viewed in the light of complications related to NBD, such as severe constipation, faecal incontinence and/or bowel-related surgical procedures.

Rectal perforation is considered the most serious side effect and the estimated incidence (from 2009) of rectal perforation due to TAI is 0,002% (one per 50 000 procedures). However, the latest data on perforation indicates a decrease to 0.0002% (one per 500 000 procedures). This may be compared to the risk for rectal perforation due to colonoscopy; 0,1% (one per 1000 procedures) and flexible sigmoidoscopy; 0,0025% (one per 40 000 procedures) respectively.

In the context of TAI with a rectal balloon catheter, perforation of the rectum may occur due to 3 major causes;

- Direct impaling trauma
- Over-inflation of the balloon
- Exaggerated hydrostatic pressure during water instillation

Perforations due to direct impaling trauma will most often be located in the rectum or in the anal canal. If the perforation affects only the extra-peritoneal perirectal space it is possible that the event will be asymptomatic and stay unrecognized. It is possible that this event may not necessitate surgery, but drainage and antibiotics instead. Should however, the intra-peritoneal space be affected, it is considered as an acute medical emergency condition that most often requires abdominal surgery with the formation of a stoma.

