Autonomic dysreflexia (AD) is a potentially life-threatening acute condition requiring immediate emergency care. AD most typically occurs in the SCI population, especially those with a lesion at or above the T6 spinal cord level. Acute AD is a reaction of the autonomic nervous system to overstimulation and is characterized by paroxysmal hypertension with throbbing headaches, profuse sweating, nasal stuffiness, flushing of the skin above the level of the lesion, slow heart rate, anxiety, and sometimes by cognitive impairment. AD is believed to be triggered by afferent stimuli (nerve signals that send messages back to the spinal cord and brain) which originate below the level of the spinal cord lesion. The most common causes of autonomic hyperreflexia seen in patients with SCI are loss of bowel and bladder function, resulting in impaction in the case of the bowels and distention in case of the bladder. Proper treatment of AD involves administration of anti-hypertensives along with immediate determination and removal of the triggering stimuli. The rectum should be cleared of stool impaction, using lubricating gel. If the noxious precipitating trigger cannot be identified, drug treatment is needed to decrease elevating intracranial pressure until further examination can identify the cause.

In the only randomized controlled study to date, investigating TAI, symptoms related to AD tended to be more common in the non-TAI group, potentially suggesting that TAI may have a protective effect against AD.

Additional difficulties that may arise during irrigation are e.g.; bleeding, pain, autonomic symptoms (sweating, palpitations and dizziness), leakage of water around the catheter/cone, difficulties inserting catheter/cone or instilling irrigant, retention of the instilled irrigant, no evacuation of stool after the TAI procedure, faecal incontinence and/or leakage of irrigant between TAI procedures.

A TAI procedure should always be carried out with caution. Bowel perforation is an extremely rare, but serious and potentially lethal complication to TAI, and will require immediate admission to hospital. A patient must contact the study investigator immediately if, during or after anal irrigation, he or she experiences any of the following:

- Severe or sustained abdominal pain or back pain, especially if combined with fever.
- Severe or sustained anal bleeding.

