#### **Adverse Device Effect**

An Adverse Device Effect (ADE) is defined as an AE causally **related** to the use of a medical device. This definition also includes:

- Adverse events resulting from insufficient or inadequate instructions for use, deployment, implantation, installation, or operation, or any malfunction of the device.
- Any event resulting from use error or from intentional misuse of the study device.

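### The causality grades overlap: an adverse event that both the device and another cause can explain fits *unrelated* and a device-related grade, and no rule says which prevails

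*Protocol*

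**What the plan says.** Section 6.3.1.1 (Causality) applies one three-level scale to every event: "All AEs are categorized as unrelated, possibly related or related, as defined below".

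- *Unrelated* can be reached in two ways. The first is that "the AE is not reasonable in relation to the use of the medical device". The second, joined by 'or', is "or another cause can itself explain the occurrence of the event".
- *Possibly related* requires that "the AE may be explained by the medical device and the onset is reasonable in relation to the use of the medical device", with the qualifier "however there is insufficient information to determine the likelihood of this possibility".
- *Related* requires that the device is the most likely explanation and that the onset fits.

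Only a *related* event becomes an ADE. The separate ADE definition in the same section also takes in events from inadequate instructions or malfunction, and "Any event resulting from use error or from intentional misuse of the study device".

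Section 6.3.1.2 has the investigator record causality for all adverse events, and has all serious events reported to the sponsor whatever the causality. Table 2 in section 2.3 names adverse events, serious adverse events and adverse device effects as safety variables.

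**The concern.** The grades of a causality scale should be mutually exclusive, or the protocol should say which one wins. Here the second route to *unrelated* is met once some other cause is able to explain the event alone, even if the device remains a good explanation.

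The overlap falls on events that matter in this trial. Every subject has a spinal cord injury and a baseline NBD score of at least 10 (section 4.2). Section 1 links spinal cord injury to incontinence and constipation. On autonomic dysreflexia, section 1.2 states that "The most common causes of autonomic hyperreflexia seen in patients with SCI are loss of bowel and bladder function". The same section lists pain, bleeding, autonomic symptoms and incontinence among the difficulties that irrigation may bring. For some of these events, the underlying condition and the device are both candidates.

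The grade carries weight because the study has one arm (section 3.3), so no control rate shows how many such events would have occurred without the device. The judgement is made by investigators at 10-12 centres in about 9 countries (section 3.1), and the wording lets two of them grade the same event differently while both follow the protocol. The scale is applied at the site when the event is recorded. A later analysis can pool *related* with *possibly related*, but that does not bring back an event already graded *unrelated*.

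**Working it through.** The protocol gives no figure to reproduce, so the check is logical.

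**Step 1. Cross the two questions that the definitions ask.**

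| | Another cause can explain the event alone | No other sufficient cause |
|---|---|---|
| Device not a reasonable explanation | *Unrelated* (both routes) | *Unrelated* (first route) |
| Device may explain it, onset fits | *Unrelated* (second route), **and** can meet *possibly related* or *related* | *Possibly related* or *related* |

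The bottom-left cell carries more than one permitted grade. It can meet *possibly related* when the likelihood of device causation cannot be settled, and *related* when the device is judged the most likely explanation. Neither definition asks that other causes be ruled out. The second route to *unrelated* says that another cause can explain the event, not that it does or most likely does.

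**Step 2. Look for a tie-break.** Section 6.3.1.1 states no order among the three grades and no default for doubt. None of the three definitions refers to the others.

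**Step 3. Trace the effect on each count when a bottom-left event is graded *unrelated*.**

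| Grade it would otherwise have had | ADE count | *Possibly related* tally | All adverse events and serious adverse events |
|---|---|---|---|
| *Possibly related* | unchanged | one fewer | unchanged |
| *Related* | one fewer | unchanged | unchanged |

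The first row leaves the ADE count alone because *possibly related* is not an ADE in any case. The last column is unchanged because section 6.3.1.2 records every adverse event and reports every serious one regardless of causality.

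**Step 4. Ask whether a size follows.** Let D be the number of events the device can explain, s the share that another cause can also explain alone, and g the share of those that sites grade *unrelated*. The number moved is D × s × g. The protocol gives none of the three. As an assumption only, take D = 30 and s between 25% and 75%:

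- g = 0: none moved.
- g = 1: from 30 × 0.25 = 7.5 to 30 × 0.75 = 22.5 moved.

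The range from 0 to 22.5 only returns the assumptions, so it is not an estimate.

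**The case against.** The strongest reply is that this is a gap in wording and no more. Several parts of it stand.

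- **No precedence for *unrelated*.** A reader might infer that every device-plausible event with a competing cause must be graded *unrelated* and drops out of both device-related grades. The text does not say so. It allows a device-related grade for the same event just as readily.
- **The word 'itself'.** The other cause must be sufficient alone. Having a spinal cord injury in the background is not enough; the investigator must judge that it fully explains this event. For leakage around the catheter or difficulty inserting it, that would be hard to argue. The overlap is therefore confined to some event types.
- **Section 1.2 on complications.** The remark that "These complications should be viewed in the light of complications related to NBD" concerns the balance of benefit and risk. It is not a grading instruction and should not be read as one.
- **Use error.** A reader might infer a contradiction, with use error counting as another cause under Causality but as an ADE under the ADE definition. The ADE definition expressly includes use error and misuse, and use error is naturally part of device use. A cross-reference is worth adding, but no loss of such events is shown.
- **Nothing is lost from the safety record.** All adverse events are recorded and all serious ones reported, so the risk is misclassification.
- **No percentage undercount.** Any such figure would be an assumption, as step 4 shows.

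What the reply does not remove is the bottom-left cell. Complete recording does not make the causality grade consistent, and the narrower reading of 'itself' leaves some events, such as autonomic symptoms or incontinence, with two permitted grades.

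**Conclusion.** The point holds as an overlap of definitions without a tie-break. Where the device may explain, or most likely explains, an event with a fitting onset, and another cause can also explain it alone, section 6.3.1.1 permits *unrelated* and permits a device-related grade. This allows inconsistent grading across sites.

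A downward bias in device-related results is possible. It would fall mainly on the *possibly related* tally, and on ADEs only for events that would otherwise be *related*. Its size cannot be derived from the protocol, because neither the share of dual-explanation events nor how sites would grade them is given.

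The conclusion rests on the wording of the three definitions and on the protocol's own account that some events listed as irrigation difficulties also arise from the subjects' condition. It does not rest on any assumed rate. The change is worth making because adverse device effects are a named safety variable in an uncontrolled study and the correction is short.

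**What to change.** In section 6.3.1.1 (Causality):

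1. Limit the second route to *unrelated* to events that another cause explains and for which the device or irrigation procedure is not a reasonable explanation. A stricter test, that any device contribution has been excluded, is not needed and would rarely be attainable.
2. Add a tie-break: *If both the device/procedure and another cause are reasonable explanations, grade at least possibly related.*
3. Cross-refer to the ADE definition so that use error, misuse and malfunction are not treated as another cause.
4. Carry the new text into the eCRF help text. Query events already graded *unrelated* only where the onset is reasonable in relation to device use.

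The cost is a protocol wording change, an eCRF help-text update and one limited query round. The reported *possibly related* and *related* rate becomes somewhat higher and less specific, since some incidental events will move up a grade. Reporting the three grades separately keeps that visible.

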#### **Device Deficiency**

A device deficiency is defined as an inadequacy of a medical device with respect to its identity, quality, durability, reliability, safety or performance. This includes malfunctions, use errors, and inadequate labelling.

#### **Adverse Device Effect**

An Adverse Device Effect (ADE) is defined as an AE causally **related** to the use of a medical device. This definition also includes:

- Adverse events resulting from insufficient or inadequate instructions for use, deployment, implantation, installation, or operation, or any malfunction of the device.
- Any event resulting from use error or from intentional misuse of the study device.

#### **Serious Adverse Event**

A Serious Adverse Event (SAE) is an AE that fulfils one or more of the following criteria:

- Led to death.
- Led to a serious deterioration in the health of a subject, that either resulted in:
  - a life-threatening illness or injury, or
  - a permanent impairment of a body structure or a body function, or
  - in-patient or prolonged hospitalization (excluding hospital admissions and/or surgical operations that were planned before or during the study, where the illness/disease existed before the subject was enrolled and did not deteriorate in an unexpected way during the study), or
  - medical or surgical intervention to prevent life-threatening illness or injury or permanent impairment to a body structure or a body function.
- Led to foetal distress, foetal death or a congenital abnormality or birth defect.

### **Serious Adverse Device Effect**

A Serious Adverse Device Effect (SADE) is defined as:

- An ADE that has resulted in any of the consequences characteristic of a serious adverse event, or
- A device deficiency that might have led to a serious adverse event if:
  - Suitable action had not been taken, or
  - An intervention had not been made, or
  - Circumstances had been less fortunate.

### **6.3.1.2 Adverse Event and Device Deficiency Reporting**

Information about adverse events will be collected at each visit following the subject's signing of the informed consent throughout the treatment period.

### **Adverse Events**

The investigator is responsible for recording the following in the CRF for **all** AEs:

- Adverse Event (i.e. the diagnosis or symptom(s))
- Start and stop date
- Whether the event is serious or not, and
- Causality
- Action taken with regard to study device
- AE Outcome

**NB!** If it is suspected that the medical device under study may have interfered with the effectiveness of a contraceptive medication/device, this should be reported as an ADE. Pregnancy itself, or elective abortions without complications, should not be reported as AEs.

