**Table 2 Safety Objectives**

| Safety Objective                                                   | Safety Variables                                                     |
|--------------------------------------------------------------------|----------------------------------------------------------------------|
| To evaluate short- and long-term safety of the product and therapy | Adverse events, serious adverse events, adverse device effects, etc. |

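### The adverse event fields in Section 6.3.1.2 include no intensity grade, so non-serious events of the same term cannot be tabulated by how severe they were

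*Protocol*

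**What the plan says.** The safety objective in Table 2 (Section 2.3) is "To evaluate short- and long-term safety of the product and therapy". The variables named for it are adverse events, serious adverse events, adverse device effects and an open-ended remainder.

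Section 6.3.1.2, under Adverse Events, sets out the data: "The investigator is responsible for recording the following in the CRF for" all adverse events. The items are the diagnosis or symptom, "Start and stop date", "Whether the event is serious or not, and" causality, "Action taken with regard to study device", and the outcome of the event. Causality has three levels under Section 6.3.1.1: "All AEs are categorized as unrelated, possibly related or related, as defined below".

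Seriousness is defined in Section 6.3.1.1 by consequence: death, life-threatening illness or injury, permanent impairment, hospitalisation, intervention to prevent a life-threatening or permanent result, or foetal harm.

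Elsewhere the protocol does speak of intensity. Section 1.2 states: "There are several side effects or problems reported with the use of TAI, though most of them are mild and of minor concern". The same section asks patients to contact the investigator at once for abdominal pain, back pain or anal bleeding that is severe or lasting. Sections 1.1 and 3.3 say that the study is meant to assess whether tailored irrigation goes with better tolerability for patients.

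**The concern.** Seriousness and intensity are different properties. A painful irrigation that leads to no admission, no lasting impairment and no preventive intervention is non-serious, however distressing it was. The difficulties that Section 1.2 lists for irrigation (bleeding, pain, sweating, palpitations, dizziness, leakage) can plausibly occur at any intensity without meeting a seriousness criterion.

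The design makes the description of harms matter. There is no comparator arm (Sections 3.1 and 3.3), and safety conclusions come from the safety analysis set (Section 7.2). They therefore rest on describing in absolute terms what happened to treated subjects. If intensity is not recorded, that description lacks a dimension that bears directly on tolerability. What a protocol leaves to the analysis plan is normally no finding, but this gap lies in data collection, and no later document can tabulate a field that was never captured.

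**Working it through.** No arithmetic on error rates, power or sample size applies. The check is a reading of every place where the protocol defines, collects or uses adverse event data.

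**Step 1. What each listed field can tell about intensity (Section 6.3.1.2).**

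| Field | Intensity grade? | Indirect information on how bad the event was |
|---|---|---|
| Diagnosis or symptom | No | Names the event only |
| Start and stop date | No | Duration |
| Serious or not | No | Marks events with the listed consequences |
| Causality (three levels) | No | None |
| Action taken with the device | No | Whether use was changed because of the event |
| Outcome | No | How the event ended |

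Of the 6 fields, 0 are an intensity grade. Leaving out the term, 6 − 1 = 5 fields allow events to be split further. Leaving out causality as well, 5 − 1 = 4 bear indirectly on how bad an event was.

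**Step 2. Whether another section supplies the grade.** The definitions in Section 6.3.1.1 cover event, causality, device deficiency, device effect, and the serious forms of event and device effect; none defines intensity. Table 2 names no intensity variable. Table 3 schedules event collection without adding fields. The severity measures that the protocol does set up concern the cord injury (ASIA) and the bowel dysfunction (NBD score), not adverse events. The app lets subjects rate irrigations (Section 5.1.2.1), but that rating is not described as grading adverse events. The Follow-up Questionnaire (Section 6.4.4) is not so described either: it covers perception, satisfaction, compliance and urinary tract infections, at 3 and 12 months or at early withdrawal.

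**Step 3. How far the indirect fields reach.** An event leading to admission or permanent impairment is flagged serious and needs an SAE report with supporting documents (Section 6.3.1.2). Pain that led to a change in device use differs from pain that did not, through the device-action field. A lasting bleed differs from a brief one through its dates. What is left is the group of non-serious events with the same term and similar duration, device action and outcome. Within that group nothing recorded distinguishes mild from severe.

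**Step 4. Set against the protocol's own use of intensity.** In the contact instruction of Section 1.2, dates can show that pain or bleeding was lasting, but no listed field shows that it was severe. The background statement that most side effects are mild cannot be compared directly with this study's non-serious events.

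**The case against.** The strongest reply has four parts.

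First, a reader might infer from the missing grade that the study can produce only counts in which trivial discomfort and disabling harm look alike. The documents do not support that. The seriousness criteria and the SAE report pick out events with grave consequences, and duration, device action and outcome separate many others. This part stands, and it confines the point to non-serious events of the same term.

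Second, tolerability does not rest on the event table alone. Reasons for discontinuation and the presence of adverse events are asked about at withdrawal (Section 4.5.2), reasons for non-compliance are to be evaluated (Section 3.1), and the Follow-up Questionnaire covers perception and compliance. This stands in part. Those sources show whether people stopped and how they viewed the therapy. Device action and stopping are weak stand-ins for intensity, because a motivated subject may continue despite severe pain while another stops for mild discomfort.

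Third, a reader might link the gap to the 45% and 55% discontinuation rates cited in Section 7.4. Those figures serve to inflate the sample size, and the protocol does not attribute them to harms, so they add nothing here. Likewise, the remark that most side effects are mild is background on irrigation in general; failing to test it breaches no stated objective.

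Fourth, the eCRF is not shown, and Section 6.3.1.2 does not say that the form holds nothing else. This stands as a limit on certainty: the form may already carry a grade.

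**Conclusion.** The point holds in a narrow form. The protocol lists no intensity grade for adverse events and supplies none elsewhere. For non-serious events of the same term, intensity therefore cannot be tabulated and can only be inferred from duration, device action and outcome. That limits, but does not defeat, the safety objective in Table 2 and the tolerability aim in Sections 1.1 and 3.3.

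Its size cannot be put in numbers: the protocol gives no expected frequency of non-serious events and no planned safety table. The primary analysis and the reporting of serious events are unaffected, and the protocol contradicts nothing of its own here. The conclusion assumes that the eCRF follows the list in Section 6.3.1.2; if it already holds a grade, only the protocol text needs alignment. This is a cheap improvement.

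**What to change.** Add an intensity field to the list in Section 6.3.1.2 and to the eCRF: mild, moderate or severe, worst grade during the event, each with a one-line definition, and a statement that intensity is distinct from seriousness. If the eCRF already has such a field, bring the list into line with it.

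Grade events already entered from source documents where these allow it, and flag those grades as retrospective. Summarise related and possibly related events by worst intensity per subject.

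The cost is one eCRF field and a short back-grading task. The drawback is that retrospective grades are less exact than those given at the time, which the flag makes visible. Treatment, visits and sample size do not change.
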